### **4.3 Benefits of the study**

The lack of vaccine effectiveness data among elderly in Thailand may be contributing to the low vaccine coverage in the elderly despite recommendations. Only 14-15% of adults  $\geq 65$  years had been vaccinated against influenza between 2010 and 2012 (46). A longitudinal cohort study assessing IIV3 effectiveness against laboratory-confirmed influenza and the duration of the humoral immune response after subsequent vaccinations will help inform policy. It will also help

close current gaps in knowledge regarding IIV3 effectiveness among the elderly and its cost effectiveness. This study will also determine the incidence of influenza-associated exacerbations of COPD among elderly participants having ARIs in the community and whether IIV3 helped alleviate them and reduced hospitalization rates. Our study will also determine if ARIs and SARIs are associated with a long term negative change in functional status among the elderly. Finally, through this study, the incidence of confirmed-RSV among elderly experiencing ARI or SARI in Thailand will be calculated so that prevention and treatment of RSV among elderly can be reevaluated.

## **5. Objectives**

### **1. Primary Objectives**

1.1: Measure the incidence of laboratory-confirmed influenza-associated ARI and SARI among a cohort of persons aged 65 years and older in 2 districts in Nakhon Phanom Province and calculate vaccine effectiveness by comparing incidence between persons who did and did not receive IIV3, controlling for potential confounders.

1.2: Assess the medical costs (direct and indirect) associated with influenza infections among the elderly and estimate the savings from vaccination based on varying levels of vaccine coverage, and evaluate the value for money of the influenza vaccine campaign program for persons aged 65 years and older

1.3: Among persons aged 65 years and older with COPD, measure the incidence of influenza-associated COPD exacerbations meeting ARI or SARI case definitions, and all-cause exacerbations and compare incidences between vaccinated and unvaccinated persons

### **2. Secondary Objectives**

2.1: Measure the effect of SARI and ARI on change in functional status

2.2: Evaluate duration of humoral immune response of IIV3 among persons aged 65 years and older; and compare difference in humoral immune response by number of past influenza vaccinations

2.3: Measure the incidence of respiratory syncytial virus in persons  $\geq 65$  years

## **6. Location and Duration**

### **6.1 Location:**

The study will be conducted in That Phanom and Plapak districts in Nakhon Phanom (NP) Province. The data that are collected will be analyzed at the Public Health Office in Muang District, Nakhon Phanom and at the MOPH in Nonthaburi. [name] from the Nakhon Phanom Public Health Office will be the primary researcher for this project. Members of the Thai Ministry of Public Health (MOPH) will be collecting and analyzing the data and laboratory specimens with help from the staff at Thailand MOPH – U.S. CDC Collaboration (TUC). Centers for Disease Control and Prevention (CDC) will work to aid MOPH in their scientific methods of the study.

### **6.2 Duration:**

We will begin recruiting and training health care workers on data collection and laboratory technique in February of 2015 until April 2015 allowing three to four months. Participants enrolled in the study will be followed for two years from June 2015 through June 2017. Patients will be followed for two years as the incidence of influenza and the effectiveness of the annual vaccine composition can vary from year to year, making conclusions from two years more reliable than one alone. Additionally, approximately six more months will be needed for data analysis. The entire study will take place for approximately 2 years and 10 months, and should be completed by December 2017.

## **7. Research Methodology**

### **7.1 Population**

The target population for this study is the elderly (aged 65 years and older) in the That Phanom and Plapak districts of Nakhon Phanom Province.

#### **7.1.1 Sex**

Both male and female participants will be included in the study in the proportion they are found in the general population.

#### **7.1.2 Age**

The participants must be at least 65 years of age as of 15 May, 2015 to qualify for the study.

#### **7.1.3 Characteristics (i.e. occupation, social status)**

Socio-economic status including occupation, level of education, and wealth will not influence study participation.

#### **7.1.4 Illness or symptoms**

Non-institutionalized participants will be enrolled regardless of health status (unless a severe acute infection or medical condition would impair their ability to participate).

#### **7.1.5 Number of participants**

Sample size for cohort: The cohort sample size is calculated assuming a 50% vaccination rate, 80% power, a probability of committing a type I error of 5% and an incidence of influenza-associated ARI of 6% per year. With an expected VE of 40% based on our population's age and past studies (12, 16, 17), the required sample size is 2,724. Given a 15% loss to follow-up, a total of 3,133 persons should be enrolled, and assuming a 10% refusal rate, a total of 3,446, or, for simplicity, 3,500 individuals need to be selected

These sample sizes were calculated in OpenEpi.com(47) using the Fleiss Method with a correction factor as follows:

Fleiss Method:

$$n_1 = \frac{[Z_{\alpha}\sqrt{(r+1)\bar{p}\bar{q}} + Z_{1-\beta}\sqrt{rp_1q_1 + p_2q_2}]^2}{r(p_1 - q_1)^2}$$

$$n_2 = rn_1$$

where  $n_1$  is the number of cases and  $n_2$  is the number of controls,  $\bar{p}$  is the average exposure in the population,  $\bar{q}$  is  $1-\bar{p}$ ,  $p_1$  is the proportion of cases with the exposure,  $q_1$  is  $1-p_1$ ,  $p_2$  is the proportion of controls with exposure and  $q_2$  is  $1-p_2$ .

To account for the use of a normal distribution to approximate a binary function, a continuity correction is applied to  $n_1$  as follows to calculate the final sample size,  $n_{cc}$ :

$$n_{1cc} = \frac{n_1}{4} \left[ 1 + \sqrt{1 + \frac{2(r+1)}{n_1 r |p_2 - p_1|}} \right]^2$$

$$n_{2cc} = rn_{1cc}$$

where  $n_{1cc}$  and  $n_{2cc}$  are the corrected sample sizes of  $n_1$  and  $n_2$ , respectively.

Sample size for changes in functional status related to ARI or SARI: We will select matched pairs and compare functional status (measured on a 10 point scale by the VES-13) three-four weeks after the onset of an influenza-associated ARI or SARI to a control who has not had an ARI or SARI. As functional status is measured on continuous scale of 1-10, a matched dependent  $t$  test is used to compute sample sizes. We have used the PROC POWER procedure in SAS

([http://support.sas.com/documentation/cdl/en/statug/67523/HTML/default/viewer.htm#statug\\_power\\_overview.htm](http://support.sas.com/documentation/cdl/en/statug/67523/HTML/default/viewer.htm#statug_power_overview.htm)) to calculate the required sample sizes. Assuming a mean score of 4 for the controls and 5 for the cases (higher VES-13 index indicates lower functional status), and standard deviation of 3 for the difference between the two means, a type I error rate of 0.05, correlation of 0.2 and power of 80%, we require 115 in matched pairs (230 in all).

Sample size for seroconversion: Seroconversion for secondary objective 2.2 will be assessed in a sub-sample of participants. We expect seroconversion rates of 30-50% among those vaccinated. In order to calculate a proportion of 50% plus or minus 5%-pts, we need 384 individuals who intend on becoming vaccinated. We will enroll them sequentially.

$$\frac{[Np(1 - p)]}{d^2 / 1.96^2 (N - 1) + p(1 - p)}$$

Where  $N$  is the population size,  $p$  is the estimated proportion,  $d$  is the absolute precision. In this study,  $N$  is the size of the elderly population in the two districts, approximately 15,000;  $p$  is 0.5 and  $d$  is 0.05.

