## **7.10 Specific consideration**

Only 384 of the 3,500 or more total participants enrolled will be participating in second objective 2.2 which involves having blood drawn periodically in order to test serological response to the inactivated trivalent influenza IIV3 vaccine. Each participant will need to have their blood drawn five times: right before receiving the influenza vaccine on day 0, and then on days 28 and 180 and 360 after receiving the vaccine; and one additional time on days 28 of subsequent vaccination in the second year. Each blood draw will be 5cc.

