**Outcome codes:**

- |                                                               |                                                    |
|---------------------------------------------------------------|----------------------------------------------------|
| 1. Interview completed                                        | 7. Absent temporarily – will try again             |
| 2. Interview partially completed – will return to finish      | 8. Moved within study area – will try to contact   |
| 3. Interview partially completed – unable to return to finish | 9. Moved outside of study area – cannot contact    |
| 4. Refused                                                    | 10. Died. Provide date of death                    |
| 5. Ineligible                                                 | 11. No one knows the participant/Cannot be located |
| 6. Absent and unlikely to return in next 7 days               |                                                    |

|                                                      |               |                                                           |
|------------------------------------------------------|---------------|-----------------------------------------------------------|
| Describe how to find the house                       |               |                                                           |
| Home phone number                                    |               |                                                           |
| Cell phone number                                    |               |                                                           |
| Is there a caregiver?                                | 1 Yes
2 No | Caregiver's name:                                         |
| Phone number for caregiver?                          |               | Circle the number that we should use for the weekly call. |
| Participant's age (years)                            |               |                                                           |
| Have you lived in Nakhon Phanom since Songkran 2014? | 1 Yes
2 No |                                                           |

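### Section 7.1.5 inflates the cohort size by multiplying by 1.15 and 1.10 instead of dividing by 0.85 and 0.90, allows nothing for ineligible or unlocatable people, and Section 7.10 calls the 3,500 selected people enrolled

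*Protocol*

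**What the plan says.** Section 7.1.5 sets the cohort size "assuming a 50% vaccination rate, 80% power, a probability of committing a type I error of 5" per cent. The event rate entered is "an incidence of influenza-associated ARI of 6% per year". The effect is given as "With an expected VE of 40% based on our population's age and past studies", the method as "using the Fleiss Method with a correction factor as follows", and the result as "the required sample size is 2,724". Allowing for 15% loss to follow-up and 10% refusal, it then states that "a total of 3,133 persons should be enrolled, and assuming a 10% refusal rate, a total of 3,446" are needed. The last figure is rounded to 3,500 people to be selected.

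Sections 7.5.1 and 7.5.2 draw the 3,500 by systematic sampling from a village listing of everyone aged 65 and over. Eligibility under Sections 7.2 and 7.3 is established afterwards, at the home visit. The visit form has outcome codes for people who are ineligible, have moved out of the area or have died, and for "No one knows the participant/Cannot be located".

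Section 7.10 gives the same number a different meaning: "Only 384 of the 3,500 or more total participants enrolled will be participating in second objective 2.2".

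**The concern.** A 15% loss is a share of those enrolled, and a 10% refusal is a share of those approached. To end with a given number, one divides by the fraction that remains. Multiplying by one plus the loss rate gives a target that is too small on the protocol's own rates.

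Refusal is also the only loss allowed for between selection and enrolment, although the protocol's own form expects others. No replacement of selected people is described. Finally, if 3,500 means people selected in one section and people enrolled in another, field teams and readers cannot tell which target applies. At stake are the enrolment and selection targets and whether the stated 80% power goes with them.

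**Working it through.** **Inputs, all from Section 7.1.5:** 6% per year, read as the incidence in the unvaccinated; effectiveness 40%, so 6% × 0.6 = 3.6% in the vaccinated; equal groups; power 80%; type I error 5%, read as two-sided because the protocol does not say; loss 15%; refusal 10%.

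**1. Base number.** Average risk p̄ = (0.06 + 0.036)/2 = 0.048. With the correct denominator, (p1 − p2)²:

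- n1 = [1.960 × √(2 × 0.048 × 0.952) + 0.8416 × √(0.06 × 0.94 + 0.036 × 0.964)]² / 0.024² = (0.5925 + 0.2540)² / 0.000576 = 1,244.2
- With continuity correction: (1,244.2/4) × [1 + √(1 + 4/(1,244.2 × 0.024))]² = 1,326.2, so 1,327 per group and 2,654 in total.

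The stated 2,724 is 70 higher (2.6%), in the conservative direction. Other readings are further away: 2,490 without the correction, 2,124 one-sided with it, and 2,098 if 6% is the overall incidence.

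**2. The protocol's inflation, reproduced.** 2,724 × 1.15 = 3,132.6, giving 3,133. Then 3,132.6 × 1.10 = 3,445.9, giving 3,446. Both match exactly.

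**3. What the stated targets retain on the stated rates.**

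- 3,133 enrolled × 0.85 = 2,663.
- 3,446 selected × 0.90 × 0.85 = 2,636.
- 3,500 selected × 0.90 = 3,150 enrolled; × 0.85 = 2,677.5 retained, about 46 below 2,724 (1.7%).

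**4. The chain by division.**

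| Base number | Enrolled (÷ 0.85) | Selected (÷ 0.90) |
|---|---|---|
| 2,724 | 3,204.7 → 3,205 | about 3,561 |
| 2,654 | 3,122.4 → 3,123 | 3,469.3 → 3,470 |

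Against 2,654, the planned 3,500 has 3,500 − 3,470 = 30 people to spare before any ineligible or unlocatable person is counted.

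**5. One-year power** (6% vs 3.6%, two-sided 5%). At 2,677.5 retained it is 80.4% with continuity correction and 82.8% without.

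**6. Ineligible or unlocatable people.** The protocol gives no rate, so the fractions are assumptions. Retained = 3,500 × (1 − fraction) × 0.90 × 0.85.

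| Assumed fraction | Retained | Power, corrected | Power, uncorrected |
|---|---|---|---|
| 0% | 2,678 | 80% | 83% |
| 5% | 2,544 | 78% | 81% |
| 10% | 2,410 | 76% | 79% |
| 15% | 2,276 | 73% | 76% |

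**7. Selected or enrolled.** If Section 7.10 were right and 3,500 were enrolled, 3,500 × 0.85 = 2,975 would be retained and both base numbers would be met. Sections 7.1.5 and 7.5.2 both treat 3,500 as the number drawn from the list.

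**8. Printed formula.** The denominator appears as (p1 − q1)², with q1 = 1 − p1. The numerator is (0.5925 + 0.2540)² = 0.717, so this gives 0.717/(0.06 − 0.94)² = 0.93, or 0.83 with 0.036 as p1. It was clearly not the formula used.

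**The case against.** The strongest reply is that two errors offset each other. The base number is somewhat too high for its stated inputs and the inflation somewhat too low, so 3,500 selected still delivers more than 2,654 at about 80% power. This stands, and it means the inflation slip alone has no operational consequence.

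Second, a count of people fully retained understates the information. Section 7.9 plans a Poisson model with person-time as the offset, so people lost part-way still contribute. This also stands. The second year matters more: with two-year risks of 1 − 0.94² = 11.6% and 1 − 0.964² = 7.1%, even 2,276 people give about 96% power on the same simple calculation. However, Section 7.1.5 works from a one-year incidence and claims no such credit. The follow-up is also not stated consistently: Section 6.2 says two years, while Section 3.1.4 describes weekly contact for one.

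Third, a reader might infer that the study will miss its target because its exclusions are common at this age. The documents do not support that. They give no ineligible or unlocatable rate, and Section 7.5.1 has volunteers survey each village for a current list, which should reduce the number not found. It would not remove people who fail the Section 7.3 criteria, because the listing records name, address and age only.

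The denominator may be a typographical or text-extraction fault and is minor either way.

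**Conclusion.** The figures are wrong as written. 3,133 and 3,446 come from multiplication where division is needed, and on the protocol's own rates 3,500 selected retains about 2,678 rather than 2,724. This part alone is small: a 1.7% shortfall against the stated number, none against the 2,654 that the stated inputs give, and about 80% one-year power.

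The missing allowance for ineligible and unlocatable people could matter more. One-year power would be 78% to 73% with continuity correction at assumed fractions of 5% to 15%. Its true size cannot be taken from the documents, and partial person-time and a second year would soften or remove the effect. A loss of power is therefore possible but not shown.

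The conflict between Section 7.10 and Sections 7.1.5 and 7.5.2 over the meaning of 3,500 is plain and needs reconciling. The power figures assume 6% against 3.6%, equal groups, a two-sided 5% test and the stated 15% and 10% losses.

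**What to change.** - Choose one base number in Section 7.1.5: either 2,654 from the stated inputs, or 2,724 with its inputs corrected. Restate the chain by division from that number only: 3,123 enrolled and 3,470 selected, or 3,205 and about 3,561. The two chains should not be mixed.
- Keep 3,500 selected, state an assumed ineligible or unlocatable fraction, and give the expected number enrolled, the number retained and the power. If the power is meant to rest on partial person-time or on two years, say so.
- Correct Section 7.10 so that 3,500 is the number selected, and use the two terms consistently in Sections 7.1.5, 7.5.2 and 7.10.
- Minor: print the denominator as (p1 − p2)².

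The cost is a few restated figures and one explicit assumption. The quoted one-year power may become slightly less favourable.

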In order to measure the impact of the first episode of ARI or SARI on functional status, we will conduct a nested case-control study of participants recovering from an ARI or SARI. Participants who experience their first ARI or SARI after enrollment will be matched with cohort participants who have not yet experienced an ARI or SARI based on age ( $\pm 5$  years), sex, influenza vaccination and most recent functional status measurement. Interviews will be conducted three to four weeks after the onset of ARI or SARI in the case and both cases and controls will be compared with respect to changes in functional status measurement (VES-13 score  $\geq 3$ ).

Elderly with COPD: In the standardized baseline questionnaire assessing functional status and medical conditions, participants will be asked whether they have been diagnosed with COPD. If they do, at the end of two years, the number of outpatient visits and inpatient admissions for exacerbations of COPD will be determined (by directly observing their medical records). A COPD exacerbation is defined as “a sustained worsening of the patient's condition, from the stable state and beyond normal day-to-day variations that is acute in onset and may warrant additional treatment in a patient with underlying COPD” (11). We will use the collected nasal self-swabs or healthcare worker collected nasopharyngeal swab taken when the participant was experiencing an ARI or SARI to confirm whether the COPD exacerbations the participant experienced were influenza-associated. At the end of the study, the incidence of all-cause COPD exacerbations and laboratory confirmed influenza-associated COPD exacerbations among the elderly with COPD who fit the ARI or SARI case definitions will be calculated. The incidence among those who were vaccinated will be compared to those who were not vaccinated.

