All participants will be provided a self-swabbing kit from the study team that includes Dacron swabs and test tubes with transport media (TM) which are already labeled with the participants' hospital number, along with written instructions. Participants will be asked to take one nasal self-swab, and to place it in the refrigerator in a separate test tube filled with 1-3ml of TM. Participants will then be asked to describe the procedure to ensure they understand the full technique and will be guided appropriately. Participants will be given a study card with their study ID number and assigned health volunteer's telephone number. Participants who experience an ARI, defined as new onset of cough or worsening of chronic cough, will be asked to take a self-swab as soon as possible and then to call their assigned health volunteer to make an appointment to have their swab collected and answer some questions for the ARI/SARI Episode Questionnaire at the time of the appointment (which will be within 24 hours). The assigned health volunteer will bring an ice box and new Dacron self-swab kit to the sick participant's home, and the specimen will be transported in the ice box by the health volunteer to the sub-district health center for temporary storage. Health volunteers will also conduct the Functional Status Questionnaire three to four weeks after the onset of a participant's ARI or SARI and the Outcomes and Costs of ARI Questionnaire 1 week after the participant recovers which will be monitored through the weekly calls and by the study team. If a participant is very ill due to an ARI and needs assistance in taking a nasal self-swab, they can ask their assigned health volunteer for help in obtaining the specimen. Health volunteers will also be trained to contact their assigned participants weekly to identify ARI events that they have not been notified of already and to take a weekly questionnaire. They will attempt three contacts, by phone or in person, at different times of the day before considering the participant to have missed the week. In the case of an ARI event, participants who have not yet taken a self-swab will be asked to self-swab immediately.

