### **For secondary objective 2.1 (Functional status)**

Participants will be scored on their VES-13 results every six months. The Vulnerable Elders Survey (VES-13) is a function-based questionnaire that was developed to screen elderly 65 years of age or greater in the community to determine their risk for health deterioration (7, 8). The questionnaire asks elderly to self-report their age, health, limitations in physical function and functional disabilities, and takes an average of less than five minutes to complete(7, 8). This tool can be administered over the phone or in person. Each response to each question on the form has a point value attached ranging from 0 to 3 points, and it is scored by adding up points based on the responses received, up to 10.(8) Scores  $\geq 3$  indicate frailty associated with increased mortality.

In order to measure the impact of the first episode of ARI or SARI on functional status, we will conduct a nested case-control study of participants recovering from an ARI or SARI. Participants who experience their first ARI or SARI after enrollment will be matched with one cohort participant who has not yet experienced an ARI or SARI based on age ( $\pm 5$  years), sex, influenza vaccination and most recent functional status measurement. Interviews will be conducted three to four weeks after the onset of ARI or SARI in the case and both cases and controls will be compared with respect to changes in functional status measurement using a multinomial logistic regression to control for other potential confounders. Beginning from January 2016, when a complete dataset for vaccination and functional status will be available, these interviews will be conducted until the required sample size of 115 matched pairs of cases and controls are met.

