| If the participant has been sick and took nasal self-swabs or had a nasopharyngeal swab taken recently, ask the following questions. Otherwise, skip to question 3. |                                                         |                                         |      |
| 1                                                                                                                                                                          | Have you recovered from your acute respiratory illness? | 1 Yes

2 No

77 Do not know |      |

|                                                                                                                                                                                                                             |                                                                        |                                                                                                                        |                                            |
|-----------------------------------------------------------------------------------------------------------------------------------------------------------------------------------------------------------------------------|------------------------------------------------------------------------|------------------------------------------------------------------------------------------------------------------------|--------------------------------------------|
| 2                                                                                                                                                                                                                           | How many days ago did you recover from your acute respiratory illness? | 1 Today
2 Yesterday
3 2 days ago
4 3 days ago
5 4 days ago
6 5 days ago
7 6 days ago
8 7 days ago |                                            |
| Mark calendar/appointment sheet to call participant 1 week after they say they recovered from their respiratory illness to take the Functional Status Questionnaire and the Outcomes and Costs of ARI Questionnaire. |                                                                        |                                                                                                                        |                                            |

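### Functional-status sub-study: 115 pairs do not follow from the SD as written, the 80% power belongs to a test other than the named analysis, and the interview is timed in two ways

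*Protocol*

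**What the plan says.** **Sizing (section 7.1.5).** The VES-13 score is treated as continuous and a matched t test is used. The inputs are: "Assuming a mean score of 4 for the controls and 5 for the cases"; a "standard deviation of 3 for the difference between the two means"; and "a type I error rate of 0.05, correlation of 0.2 and power of 80%, we require 115 in matched pairs (230 in all"). The comparison is described as made "three-four weeks after the onset of an influenza-associated ARI or SARI to a control who has not had an ARI or SARI".

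**Analysis.** Section 7.5.1, under secondary objective 2.1, says that cases and controls will be "compared with respect to changes in functional status measurement using a multinomial logistic regression", adjusting for other confounders. Section 3.1.4 says that "both cases and controls will be compared with respect to changes in functional status measurement (VES-13 score" of 3 or more, in brackets). Section 7.9 describes a matched comparison without naming a model.

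**Timing.** Section 7.5.1 has health volunteers "conduct the Functional Status Questionnaire three to four weeks after the onset of a participant's ARI or SARI". Section 3.1.4, the secondary objective 2.1 text and section 7.5.3 give the same interval; section 7.5.2 says within that interval. Form 4c, the weekly contact form, tells the volunteer to "call participant 1 week after they say they recovered from their respiratory illness to take the Functional Status Questionnaire", together with the cost questionnaire.

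**Cases.** Objective 2.1 and sections 3.1.4, 7.5.1, 7.5.2 and 7.9 refer to ARI or SARI without requiring an influenza result. Only the sizing paragraph says influenza-associated.

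**The concern.** If 3 is already the SD of the pair difference, the correlation of 0.2 has nothing left to do in a paired t test, yet it is listed as an input. One of the written inputs therefore cannot mean what it says, and a reader cannot tell from the text whether the sub-study is oversized or correctly sized.

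The 80% is attached to a paired t test on the score, but the methods text commits to a different model and the summary to a cut-off. The protocol gives no outcome categories or expected proportions for either, so the power statement does not describe the analysis that is named.

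The timing conflict affects what is measured. Volunteers work from the form. If they follow it, the interval from onset to interview depends on how long the illness lasted, so short-term effects and lasting decline are mixed and timing is tied to illness length. The 1-point difference in the sizing is stated for 3 to 4 weeks after onset.

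**Working it through.** **Inputs (section 7.1.5).** Difference 5 − 4 = 1 point; SD 3; correlation ρ = 0.2; type I error 0.05; power 80%. Sidedness is not stated. I take two-sided, because that reproduces the plan's figure; one-sided gives 91 pairs.

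**1. Reproducing 115 pairs: 3 as the SD of each score**

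- SD of the pair difference = √(2 × SD² × (1 − ρ)) = √(2 × 9 × 0.8) = √14.4 = 3.795.
- Normal approximation: n = (1.960 + 0.842)² × 14.4 / 1² = 7.849 × 14.4 = 113.02, so 114 pairs.
- Exact noncentral t: 115 pairs, with power 80.0%. This matches the plan.

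**2. The wording taken literally: 3 as the SD of the difference**

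- Normal approximation: n = 7.849 × 9 = 70.64, so 71 pairs.
- Exact noncentral t: 73 pairs. At 115 pairs, power is 94.3%.

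The two readings coincide only at ρ = 0.5, where √(2 × 9 × 0.5) = 3.0. At the stated ρ = 0.2, an SD of 3 for the difference would imply a per-score SD of 3 / √1.6 = 2.37.

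**3. Sensitivity of the paired t test at 115 pairs, per-score SD 3**

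| Correlation | SD of difference | Pairs for 80% | Power at 115 |
|---|---|---|---|
| 0 | 4.243 | 144 | 70.8% |
| 0.1 | 4.025 | 130 | 75.2% |
| 0.2 | 3.795 | 115 | 80.0% |
| 0.3 | 3.550 | 101 | 85.0% |
| 0.5 | 3.000 | 73 | 94.3% |

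**4. Test sized against test named**

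| Place | Outcome | Method |
|---|---|---|
| 7.1.5 | VES-13 score, continuous | Paired t test |
| 7.5.1, objective 2.1 | Change in functional status, categories not given | Multinomial logistic regression |
| 3.1.4 | Change, with a cut-off of 3 or more in brackets | Not named |
| 7.9 | Change in functional status | Matched comparison, model not named |

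Only the first row has a stated power. For the second, the categories and their expected proportions would be needed, and the protocol gives neither.

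**5. Timing**

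Let L be the illness length in days. Form 4c puts the interview at day L + 7 after onset; the body text puts it at day 21 to 28. They agree when 21 ≤ L + 7 ≤ 28, that is 14 ≤ L ≤ 21. A 5-day illness is assessed on day 12 under the form, which is 9 to 16 days before the body text's window.

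**The case against.** **The SD slip changes no number.** This stands. The plan's 115 pairs reproduce exactly, and the literal reading gives more power. It is a labelling error and should not be presented as a sample-size failure.

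**The details of the regression belong in an SAP.** This stands in part. How the outcome is categorised and how the matching enters the model may properly be left there. The protocol does not say that pairs will be broken, and section 7.9 keeps the matched comparison, so it should not be read as ignoring the pairing. What remains is that the protocol itself names both a sizing test and a different model.

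**A reader might infer that the 80% power does not hold and that about half of it is lost.** The documents do not support that. As an illustration only, take a McNemar test on a score of 3 or more at 115 pairs. Bivariate normal scores with means 4 and 5, SD 3 and correlation 0.2 give about 49 to 52% (219 to 237 pairs for 80%). The plan names no such test, and the normal assumption puts about 9% of controls below 0 on a 10-point scale. A bounded 0 to 10 distribution (beta-binomial) with the same means and SD gives about 61%. Pairs are matched on the latest VES-13, which may raise the correlation above 0.2; at 0.5 to 0.7 the figures are 59 to 73% (normal) and 71 to 81% (bounded). Categorising probably costs power, but a range of 49 to 81% shows that its size depends on assumptions that the protocol does not supply.

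**The timing error is one line on one form.** True, and controls are interviewed at the same time as their case (section 7.5.2), so the within-pair contrast stays contemporaneous. The interval since onset would still vary with illness length if the form were followed. No power loss can be derived from this.

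**Conclusion.** The point holds as an inconsistency between written inputs, sizing test, named analysis and data-collection form.

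- **SD.** As written, the input gives 73 pairs, or 94.3% power at 115. The stated 115 pairs at 80.0% require 3 to be the SD of each score. There is no shortfall. This assumes a two-sided 0.05 test.
- **Power.** The 80% is correct for the paired t test on the score with a per-score SD of 3 and correlation 0.2. It is not shown for multinomial regression or for a cut-off of 3. It would probably be lower if the score is categorised, by an amount that cannot be computed from the document.
- **Timing.** The two rules agree only for illnesses of about 14 to 21 days. This is the one item with a direct effect on data collection.
- **Case definition.** The influenza-associated wording in the sizing paragraph is a minor slip against the definition used everywhere else.

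This is worth correcting, in proportion to a secondary objective.

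**What to change.** 1. In section 7.1.5, restate the input as an SD of 3 for the VES-13 score in each group with within-pair correlation 0.2 (SD of the pair difference about 3.8), two-sided.
2. Make the paired comparison of the VES-13 score, adjusted for confounders, the main analysis for objective 2.1, so that analysis and sizing agree. Keep a categorised outcome as secondary, with a method that respects the matching. Alternatively, keep the regression as the main analysis and state that the 80% applies only to the paired t test.
3. Reconcile form 4c with sections 3.1.4, 7.5.1 and 7.5.3 on when the functional questionnaire is given, and bring the wording of section 7.5.2 into line. The cost questionnaire needs no change: form and body agree on 1 week after recovery.
4. In section 7.1.5, replace the influenza-associated wording with the any-first-ARI-or-SARI definition used elsewhere.

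The cost is a few sentences in the protocol and one line on form 4c. The target stays at 115 pairs.
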